The relationship between UTIs and acute cardiovascular events is less well studied than for RTIs. Only one previous study has examined this relationship. Smeeth *et al* used the self-controlled case series (SCCS) method to analyse data from the General Practice Research Database. They found increased rates of MI and stroke subsequent to UTI, with the risk being highest in the first 3 days.^6^ However, the data analysed are almost 20 years old, and there have been no attempts to replicate the findings. Furthermore, the study defined UTI using clinical codes only, so it is unclear if the reported associations related to individuals with clinical symptoms alone, or symptoms and bacteriuria, making it difficult to interpret whether individuals had true UTIs, or whether non-specific symptoms were misdiagnosed as UTI but represented early signs of a cardiovascular event. In addition, other studies have found that roughly two-thirds of women suspected to have UTI on presentation to primary care have no evidence of UTI on microbiological culture.^20^ Therefore, the use of clinical codes alone to define UTI may lead to bias from misclassification of the exposure.

Therefore, the aim of this study is to determine whether there is a causal relationship between UTI and acute MI or stroke by analysing linked general practice, hospital admission and microbiology data, from a representative sample of the Welsh population. We will use the SCCS method, which controls for time-invariant confounding, enabling us to more reliably draw causal inferences between UTI and acute MI or stroke, compared with between-individual study designs.

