## Methods and analysis

### Aims and objectives

The specific objectives of this research are to:

Estimate incidence rate ratios (IRRs) for acute MI and stroke in the 90 days following a clinically suspected and microbiologically confirmed UTI compared with baseline (all times outside of the 90-day risk period).Assess the effect of different methods of UTI ascertainment on estimated rate ratios (ie, clinically suspected and microbiologically confirmed; clinically diagnosed only; clinically suspected but not supported by microbiology and UTI diagnosed and treated in hospital).Investigate whether the effect of a clinically suspected and microbiologically confirmed UTI on acute MI and stroke differs according to the infecting organism.

Our primary hypothesis is that a clinically suspected and microbiologically confirmed UTI will increase the risk of acute MI or stroke in the 0–90 days postinfection period.

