	As both MI and stroke have relatively high death rates, the length of the observation period is dependent on events, and no further exposures are possible after death.	Use an event-dependent observation period model extension^38^ and conduct a sensitivity analysis that repeats the analysis, excluding individuals who died within 30 days of the event.	Bruer *et al* used the event-dependent observation period model extension in their study on the association between antipsychotic drugs and myocardial infarction.^39^ Langan *et al* studied the risk of stroke following herpes zoster. They conducted a sensitivity analysis excluding individuals who died within 90 days of stroke.^40^
Event rates are constant within defined periods	MI and stroke are more common in older individuals and may be affected by seasonal changes.	Control for age and season effects.	Grave *et al* studied the association between seasonal influenza vaccination and Guillain-Barré syndrome. They adjusted for calendar month, as the vaccinations are seasonal by design.^41^ In a study of the association between chickenpox and stroke, Thomas *et al* adjusted for age in 5-year age bands.^42^
Events are independently recurrent or rare.	MI and stroke are not independent: once an individual has a first event, they are more likely to have a second.	Study first events only.	Langan *et al* began the observation period 12 months into follow-up time to ensure first stroke events had been correctly identified.^40^

MI, myocardial infarction; UTIs, urinary tract infections.

A diagrammatic representation of observation time for an individual in the proposed SCCS design is given in figure 1. Risk periods start on the date of an UTI and end 90 days later. The date of an UTI is the earliest date of occurrence of any of the events necessary for each different UTI definition. For example, the definition of UTI in our primary analysis is a combination of an UTI-related diagnostic code and antibiotic prescription in WLGP data and a urine culture result that supports a diagnosis of UTI in the WRRS data, occurring within a 7-day window. In this case, the date of the UTI would be the date of whichever of the following events occurred first: UTI-related diagnostic code, antibiotic prescription, supporting urine culture.

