### Exposure

The exposure of interest is an UTI. The risk period is 0–90 days following an UTI. This period was chosen as previous research has shown an increase in acute MI and stroke risk in the 1–90 days following an UTI.^6^ There will be a prerisk period of 7 days before the risk period, to allow for the situation where an individual has an UTI for several days prior to consultation, so events in this period are not erroneously attributed to the baseline period. Individuals can be exposed to an UTI more than once during the observation period. Each exposure will be followed by the same 90-day risk period. Baseline periods are all other times.

To ascertain UTI, we developed definitions that reflected the Public Health Wales Microbiology Division’s standard operating procedure for the investigation of urine.^36^ These procedures are followed by NHS microbiology laboratories across Wales. For each definition, the data sources required and the clinical scenario represented is summarised in table 2, and the code lists used are given in online supplemental material B–D. In our primary analysis, an individual will be regarded as being exposed to an UTI if the following events occur within a 7-day window:

A General Practice (GP) record of an UTI diagnostic or symptom code.A GP record of an antibiotic prescription.A microbiology record of a urine sample with bacterial growth of a single organism of ≥1x10^8^ colony-forming units (CFU) per litre and white cell count (WCC)≥1x10^8^/L. If there are two organisms grown, both must demonstrate growth of ≥1x10^8^ CFU per litre. More than two organisms will be regarded as mixed growth and thus not supportive of an UTI diagnosis. In a sensitivity analysis, we will widen the microbiological criteria and include all urine samples with bacterial growth of a single organism of ≥1x10^7^ CFU per litre, irrespective of the WCC.

**Table 2 T2:** Definitions of UTI for primary and secondary analyses. As the UTI definitions are combinations of two or more components, the start of the risk period is defined as the date of the earliest component

	UTI-related read code in GP data (online supplemental material B)	Antibiotic prescription in GP data (online supplemental material C)	UTI-related ICD-10 code in PEDW (online supplemental material D)	Urine culture results in WRRS	Time frame	Clinical scenario

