Primary analysis	Yes	Yes	No	Yes, showing bacterial growth of ≥1x10^8^ CFU/L and WCC ≥1x10^8^ /L	Three codes occur within a 7-day window	GP clinically suspected and microbiologically confirmed UTI
Secondary analysis 1	Yes	Yes	No	Yes, showing mixed bacterial growth (any descriptor for ‘mixed growth’ or >3 organisms).	Three codes occur within a 7-day window	GP clinically suspected UTI with mixed growth
Secondary analysis 2	Yes	Yes	No	No	Same day	GP clinically diagnosed and treated UTI. It is important to consider this group as not all individuals with suspected UTI have urine culture, and limiting to those with culture is subject to selection bias.
Secondary analysis 3	Yes	Yes	No	Yes, showing bacterial growth of <1x10^7^ CFU/L.	Three codes occur within a 7- day window	UTI is clinically suspected but not supported by microbiology. This group is important to understand if early symptoms and signs of acute MI or stroke are attributed to UTI.
Secondary analysis 4	No	No	Yes	Yes, showing bacterial growth of ≥1x10^8^ CFU/L and WCC ≥1x10^8^ /L	Two codes occur within a 7-day window	UTI diagnosed and/or treated in hospital
Secondary analysis 5	Yes, OR ICD-10 code	Yes, OR ICD-10 code	Yes, OR: UTI Read code AND antibiotic Read code	Yes, showing bacterial growth of ≥1x10^8^ CFU/L and WCC ≥1x10^8^ /L	Two/three codes occur within a 7-day window	GP clinically suspected and microbiologically confirmed UTI or UTI diagnosed and/or treated in hospital

GP, General Practice; ICD-10, International Classification of Disease version 10; PEDW, Patient Episode Database for Wales; UTI, urinary tract infection; WCC, white cell count; WRRS, Welsh Results Reporting Service.

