### Statistical analysis

We will describe the demographics of the study population, such as age and sex distribution, medical history and prescribed medication, using means and SDs for continuous variables, and frequencies and proportions for categorical variables. For each analysis, we will use conditional logistic regression to estimate IRRs, with 95% CIs, for the risk of acute MI or stroke in prerisk and risk periods compared with baseline periods. We will include only individuals who have experienced both the outcome and the exposure, and will include only the first acute MI or stroke diagnosis in the observation period. The IRRs will be adjusted for time-varying confounders: age, season and year of UTI diagnosis. Year of UTI diagnosis is included because diagnostic and coding practices may have changed over time as a result of guidance and awareness around microbial resistance. Adjusted IRRs will be reported for the risk of acute MI or stroke at 1–7, 8–14, 15–28 and 29–90 days after UTI. We will conduct the analysis in R, using the SCCS package. We will report the findings in accordance with REporting of studies Conducted using Observational Routinely-collected Data (RECORD) and STrengthening the Reporting of OBservational studies in Epidemiology (STROBE) guidelines.

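### A UTI needs three records within 7 days but is dated at the first, so an MI or stroke in the gap can change whether it qualifies and bias the 1–7-day IRR in either direction

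*Protocol article*

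**What the plan says.** In the Exposure section of the Protocol article, "an individual will be regarded as being exposed to an UTI if the following events occur within a 7-day window": a GP diagnostic or symptom code, a GP antibiotic prescription, and a urine sample meeting the growth and white-cell criteria. Table 2 gives the time frame for the primary analysis, and for secondary analyses 1 and 3, as "Three codes occur within a 7-day window". Secondary analysis 2 (GP code and antibiotic, no culture) requires both records on the same day.

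The dating rule appears twice. The Table 2 caption says "the start of the risk period is defined as the date of the earliest component". Study design says "The date of an UTI is the earliest date of occurrence of any of the events necessary for each different UTI definition", and for the primary definition "the date of the UTI would be the date of whichever of the following events occurred first".

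The primary hypothesis is that a confirmed UTI "will increase the risk of acute MI or stroke in the 0–90 days postinfection period". Under Statistical analysis, "Adjusted IRRs will be reported for the risk of acute MI or stroke at 1–7, 8–14, 15–28 and 29–90 days after UTI". Only people with both an outcome and a qualifying exposure are analysed, and only their first event counts.

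**The concern.** Under this rule, risk time opens on day 0 but the UTI exists only if further records follow, up to about a week later. In a self-controlled case series, whether a person counts as exposed should not depend on the event. Table 1 accepts this assumption. Between the first and last record it can fail in two ways:

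- **Downward.** Admission or death may mean that an outstanding GP code or prescription is never recorded. The UTI then does not qualify. The case drops out or, if the person has another qualifying UTI, the event counts as baseline. Both lower the early IRR.
- **Upward.** A urine culture taken during the MI or stroke admission may complete a UTI that the GP suspected and treated but that would otherwise have stayed unconfirmed. The event then creates its own exposure.

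The days affected matter. Of the one earlier study of UTI, the Introduction says: "They found increased rates of MI and stroke subsequent to UTI, with the risk being highest in the first 3 days". Objective 2 also compares IRRs across methods of ascertainment. Secondary analysis 2 has no gap, so part of any difference between it and the culture-based definitions could come from dating alone.

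**Working it through.** **Does any planned step cover the gap?**

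- The prerisk period (7 days, or 14 in a sensitivity analysis) lies before the first record, not between the first and the last.
- The event-dependent observation extension and the exclusion of deaths within 30 days deal with death, not with a non-fatal admission that interrupts GP records or prompts a culture.
- No item under Sensitivity and subgroup analyses dates the UTI differently or separates these days.

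**The plan's own figure.** The plan gives no figure for this bias. The nearest is 90% power for an IRR of 1.3 over a 90-day window. The inputs are 10% of cases exposed (5166 MI, 5815 stroke), alpha 0.05 taken as two-sided, and sex-weighted mean observation of 0.628 × 3251 + 0.372 × 2981 = 3151 days for MI and 0.494 × 2981 + 0.506 × 2796 = 2887 days for stroke. The signed-root likelihood-ratio formula for case series then gives 91.9% for MI and 95.9% for stroke. The statement is fair, and it concerns the 90-day window, not the first week.

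**Downward bias.** The documents state none of the following, so all are assumptions:

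- q: share of UTIs whose last record comes after day 0
- d: day of the last record, counting the first as day 0
- b: probability that an event before the last record prevents completion

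Days 1 to d − 1 fall in the 1–7-day window before completion. Days 0 to d − 1 fall in the 91-day window. With an even rate within each window:

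- 1–7-day multiplier = 1 − q·b·(d − 1)/7
- 0–90-day multiplier = 1 − q·b·d/91

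For q = 25%, d = 3, b = 1, these are 1 − 0.25 × 2/7 = 0.93 and 1 − 0.25 × 3/91 = 0.992.

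| Completed late | Day of last record | b | 1–7-day multiplier | True 2.0 reads | 0–90-day multiplier |
|---|---|---|---|---|---|
| 0% | all on day 0 | any | 1.00 | 2.00 | 1.000 |
| 10% | 2 | 1 | 0.99 | 1.97 | 0.998 |
| 25% | 3 | 0.5 | 0.96 | 1.93 | 0.996 |
| 25% | 3 | 1 | 0.93 | 1.86 | 0.992 |
| 50% | 4 | 1 | 0.79 | 1.57 | 0.978 |
| 50% | even over 1–6 | 0.5 | 0.91 | 1.82 | 0.990 |
| 50% | even over 1–6 | 1 | 0.82 | 1.64 | 0.981 |
| all | even over 0–6 | 1 | 0.69 | 1.39 | 0.967 |

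A bounding case, with every UTI completed on day 6 and every intervening event lost, gives 0.29 and 0.934.

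**Upward bias.** A Monte Carlo case-series simulation (4 million cases, 3000 days) used a true 1–7-day IRR of 2.0 with half of UTIs completed late, evenly over days 1–6. It also assumed as many unconfirmed GP-treated UTIs as confirmed ones, with a share h of those followed by an admission in the first week gaining a positive hospital culture.

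| b | h | 1–7-day IRR reads |
|---|---|---|
| 0.5 | 0 | 1.82 |
| 0.5 | 10% | 1.99 |
| 0.5 | 30% | 2.36 |
| 1 | 0 | 1.66 |
| 1 | 10% | 1.82 |
| 1 | 30% | 2.13 |

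The rows with h = 0 agree with the formula (1.82 and 1.64). The other rows show that the sign can reverse.

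**The case against.** A reader might infer that an event before the last record stops the UTI qualifying, and hence that the early IRR is biased downward. The documents do not support this. They require only that the records fall within 7 days; nothing says that they must precede the event. The Data section says that the microbiology source covers tests from both primary and secondary care, so admission does not block the culture, and a sample already sent still yields a result. Loss is likely mainly when a GP code or prescription is outstanding, or after death. A hospital culture can work the other way. This part of the objection stands, and neither direction can be assumed.

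It can also be said that:

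- The main result is barely touched, because the primary hypothesis covers 0–90 days and 1–7 days is one of four sub-windows. This stands.
- The primary analysis and secondary analyses 1 and 3 share the same three-record rule, so the unlike comparison is confined to secondary analysis 2. This stands as regards the rule.
- Earliest-record dating is a sensible proxy for onset and fits the stated aim of keeping post-onset events out of baseline. This stands too, and is why the main analysis need not change.

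None of this removes the dependence of exposure on the event within the gap, and uncertainty about its sign is itself a reason to check.

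**Conclusion.** The concern holds as a risk of event-dependent ascertainment between the first and last record, affecting the 1–7-day IRR and the comparison of secondary analysis 2 with the culture-based definitions. Direction and size cannot be fixed from the document. With complete loss of events strictly between the records, the 1–7-day multiplier is about 0.93 at q = 25%, d = 3, and runs from about 0.99 (q = 10%, d = 2) to 0.79 (q = 50%, d = 4). Partial loss brings it closer to 1, and completion by hospital cultures can take it above 1. If all records share a date there is no bias. The document does not say whether a culture is dated by sample or by result, which bears directly on the gap. These figures assume an even rate within each window; an excess concentrated in the first 3 days would make the loss larger.

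The 0–90-day IRR changes by about 1–3% at most under moderate lags, so this does not undermine the primary hypothesis. Nor do the documents show that the culture-confirmed IRR will be smaller than the same-day clinical one; they show only that the two are not built alike.

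**What to change.** Keep earliest-record dating as the main analysis. Tabulate the first-to-last gap for the primary definition and secondary analyses 1 and 3, stating which culture date is used. Add two items to the list under Sensitivity and subgroup analyses:

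- **(a)** Place the days from the first through the last record in their own stratum, neither risk nor baseline, with the sub-windows still counted from the earliest record. This takes events in the gap out of the 1–7-day estimate whichever way they act.
- **(b)** Restrict to UTIs with all records on the same day, for a like-for-like comparison with secondary analysis 2.

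The cost is one extra stratum, one restricted run and one table. In (a), some early post-onset days leave the first risk window for UTIs with delayed records, which is why it should be a sensitivity analysis and not a replacement. In (b), precision is lower. If the table shows gaps that are nearly all zero, it settles the matter.

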In secondary analysis 1, we will estimate the risk of MI and stroke among individuals with a GP record of an UTI code and antibiotic prescription, and a microbiology record of a urine sample with mixed bacterial growth (any descriptor for ‘mixed growth’ or >3 organisms). This is an important analysis given the uncertain clinical significance of mixed bacterial growth in an individual with symptoms of UTI. In secondary analysis 2, an individual will be regarded as exposed to UTI with only a GP record of a diagnostic or symptom code and an antibiotic prescription (no microbiology). Secondary analysis 3 will estimate the risk of MI and stroke among individuals where UTI was suspected and treated by the GP, but urine microbiology showed bacterial growth of<1x10^7^ CFU per litre (not supportive of an UTI diagnosis). Secondary analysis 4 will focus on individuals with a hospital admission with an UTI-related ICD-10 code and a microbiology record of a urine sample with bacterial growth of a single organism of ≥1x10^8^ CFU per litre and white blood cells ≥1x10^8^ per litre. As for the primary analysis, if there are two organisms grown, both must demonstrate growth of ≥1x10^8^ CFU per litre, and more than two organisms will be regarded as mixed growth. Secondary analysis 5 combines the primary analysis, and secondary analysis 4, considering individuals with either a GP record of an UTI code and antibiotic prescription, or a hospital admission with an UTI-related ICD-10 code, and a microbiology record of a urine sample with bacterial growth of a single organism of ≥1x10^8^ CFU per litre and white blood cells ≥1x10^8^ per litre. In the primary analysis, any hospital diagnosed UTI is likely to count towards baseline time, whereas they would be included in exposed time here.

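### Secondary analysis 3 sets no order between antibiotic and urine sample, so low-growth cultures taken on treatment can enter the group and blur what it says about misattributed MI or stroke symptoms

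*Protocol article*

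**What the plan says.** All of the following is in the protocol article.

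- **Components (Exposure, Table 2).** The culture entry for secondary analysis 3 reads "Yes, showing bacterial growth of <1x10^7^ CFU/L". Unlike the primary definition, it has no white cell count condition. The text below the table describes people in whom "UTI was suspected and treated by the GP, but urine microbiology showed bacterial growth of<1x10^7^ CFU per litre", so every episode in the group was treated.
- **Time frame (Table 2).** The rule is the same as for the primary analysis: "Three codes occur within a 7-day window".
- **Date rule.** The Table 2 caption, which covers all definitions, says "the start of the risk period is defined as the date of the earliest component". The worked example for the primary definition (Study design) dates the UTI by "whichever of the following events occurred first: UTI-related diagnostic code, antibiotic prescription, supporting urine culture". The prescription may therefore precede the culture.
- **Label and purpose (Table 2).** The clinical scenario is given as "UTI is clinically suspected but not supported by microbiology", followed by the reason for the analysis: "This group is important to understand if early symptoms and signs of acute MI or stroke are attributed to UTI".

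The list under Sensitivity and subgroup analyses does not vary the order of the components. The strengths and limitations box says in general terms that UTI diagnoses carry caveats, but does not mention antibiotic treatment before sampling.

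**The concern.** A low-growth culture is informative about the absence of infection only if the urine was collected before treatment could suppress growth. That antibiotics do this is general microbiological knowledge; the protocol does not state it. Under the unordered window, a person with a true UTI who was prescribed an antibiotic on day 0 and sampled some days later can meet the definition of secondary analysis 3.

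The same unordered window applies to the primary definition, but the consequence differs. There, late sampling can only lose true positives, because a culture that is positive on treatment is still positive. In secondary analysis 3, late sampling changes what the group represents.

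At stake is interpretation. The Introduction criticises the earlier study because symptoms coded as UTI may have been early signs of a cardiovascular event, and comparing methods of ascertainment is a stated objective. Secondary analysis 3 is the definition given the task of examining this. If it mixes treated true infections with misattributed symptoms, its IRR answers neither question cleanly.

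**Working it through.** The plan gives no figure for this point, so there is none to reproduce. The check has three steps.

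**1. Which orders does the rule admit?** Take the window as days 0 to 6 and consider the antibiotic day and the culture day. There are 7 x 7 = 49 combinations: 21 with the culture before the antibiotic, 7 on the same day and 21 with the culture after. All 49 are admitted. This counts permitted orders; it does not estimate how often each occurs.

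**2. How would treated true UTIs move the IRR?** Let *c* be the share of the group's episodes that are treated true UTIs. As a simple approximation, with episodes weighted by their expected baseline events:

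IRR(group) = *c* x IRR(true UTI) + (1 − *c*) x IRR(other episodes)

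The document does not give *c*, so 5–30% is assumed. The value 1.3 is the detectable IRR under Sample size and power. The values 1.5, 2.0 and 3.0 are assumptions.

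| *c* | true UTI 1.3, other 1.0 | true UTI 2.0, other 1.0 | true UTI 1.5, other 3.0 |
|---|---|---|---|
| 0% | 1.00 | 1.00 | 3.00 |
| 5% | 1.015 | 1.05 | 2.925 |
| 10% | 1.03 | 1.10 | 2.85 |
| 20% | 1.06 | 1.20 | 2.70 |
| 30% | 1.09 | 1.30 | 2.55 |

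For example, 0.10 x 2.0 + 0.90 x 1.0 = 1.10, and 0.10 x 1.5 + 0.90 x 3.0 = 2.85. The first two columns create an apparent excess where the other episodes have none. The last column dilutes a real misattribution signal. The bias can go either way.

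**3. How plausible is that range of *c*?** The only related figure is in the Introduction: roughly two-thirds of women with suspected UTI in primary care have no evidence of it on culture. Suppose that this carries over, that the remaining third have true UTI, that a share *q* of samples follow the antibiotic, and that each such culture is fully suppressed. Then

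*c* = (*q*/3) / (2/3 + *q*/3) = *q*/(2 + *q*), so *q* = 2*c*/(1 − *c*).

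- *c* = 5% needs *q* = 0.10/0.95 = 11%.
- *c* = 10% needs *q* = 0.20/0.90 = 22%.
- *c* = 20% needs *q* = 0.40/0.80 = 50%.
- *c* = 30% needs *q* = 0.60/0.70 = 86%.

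Incomplete suppression would require a larger *q* for the same *c*. The lower part of the range is therefore easier to reach than the upper part.

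**The case against.** The strongest case on the other side has four parts.

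- **The size is unknown and may be small.** The document does not say how many samples follow the prescription. If 10% do, step 3 gives *c* = 0.10/2.10 = 4.8%, and the group would read about 1.01 (true-UTI IRR 1.3) or 1.05 (IRR 2.0). A prescription date is also not a first-dose date. This stands: the claim is that treated infections can enter, not that many do.
- **The plan has other evidence on misattribution.** A reader might infer that secondary analysis 3 is its only safeguard. It is not. The primary definition requires microbiological confirmation, and IRRs are reported for 1–7, 8–14, 15–28 and 29–90 days, so early symptoms coded as UTI should cluster in the first window.
- **No decision depends on this IRR being 1.** A reader might infer that contamination will push the IRR above 1 and so discredit a true primary finding. The documents do not support that. They set no such rule, and the label says that microbiology does not support a UTI, not that infection is absent. With a true-UTI IRR of 1.3, a group reading of 1.015–1.09 would still lie well below the primary result. The third scenario in the table goes the opposite way.
- **The remedy needs a date that may not exist.** The article does not say whether the WRRS date is collection, receipt or report. If it is not collection, the order cannot be checked directly, and a strict rule would drop samples that were taken in time. This stands and shapes the fix.

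None of this removes the gap. Table 2 fixes the definition, so the open order is a stated rule and not a detail left to a fuller plan, and no listed sensitivity analysis tests it.

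**Conclusion.** The concern holds in limited form. As defined, secondary analysis 3 admits low-growth cultures taken after antibiotic treatment began. Treated true UTIs can therefore blur what the group shows about misattributed early symptoms, in a direction that depends on the relative IRRs of the two kinds of episode. The shifts tabulated above rest on an assumed share, assumed IRRs and a linear mixture, and they are illustrations, not estimates. The conclusion also rests on antibiotics suppressing culture growth, which the protocol does not state. The point concerns the interpretation of one secondary analysis and does not undermine the primary estimate or the stated power. It is worth acting on because the change is cheap and would show how large the problem is.

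**What to change.** 1. State which date the WRRS supplies. If only a receipt or report date is held, say so as a limitation of secondary analysis 3.
2. If a collection date is held, tabulate for this analysis how many samples were collected before, on and after the prescription date.
3. Add a sensitivity analysis of secondary analysis 3 limited to samples collected on or before the prescription date, with no other antibiotic prescription in the preceding 7 days. Report the number of episodes excluded.
4. Give the excluded episodes their own exposure category. Otherwise their time would fall into baseline, as the Exposure section already notes is likely for hospital-diagnosed UTI in the primary analysis.

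This needs date conditions on data already linked, plus one extra exposure level. The cost is fewer episodes and less precision in that sensitivity analysis. The primary analysis and the existing definition of secondary analysis 3 can stay as they are.
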